### Intervention

2.5

The training interventions will consist of 2 sessions per week for 8 weeks conducted on non-consecutive days. Irrespective of intervention arm (not including the wait-list control), in Week 1, participants start with 2 × 30-min sessions, then 2 × 45-min sessions in Week 2, followed by 2 × 60-min sessions from Week 3 onwards (inclusive of warm up and cool down), to allow for gradual and more appropriate exposure of the training stimulus.

#### Physical training

2.5.1

The participants will cycle on a recumbent bike ergometer (CXP Target Training Cycle, Matrix Fitness, Australia) for up to 45 min at the desired intensity (plus 10-min warm-up and 5-min cool-down) at a fixed intensity. This intensity is relative to their age-predicted heart rate max and rate of perceived exertion (RPE) in accordance with moderate intensity parameters (37) and tolerability as determined by their submaximal exercise assessment. Participants will cycle at a moderate intensity equivalent to 60–70% of their age-predicted heart rate maximum and/or a rate of perceived exertion that corresponds to moderate intensity on the 6–20 Borg scale (11–13) with a one-point buffer on either side (37, 38). The 30-min sessions in Week 1 will consist of a 10-min warm-up, 15 min moderate intensity bout, and 5-min cool down. Proceeding sessions follow the same warm up and cool-down timeframe, but the bout of moderate intensity exercise in the middle increases accordingly. While cycling, the tablet mounted to the bike displays a YouTube playlist of videos curated with emotionally neutral content at the digression of the participant. This is employed to replicate the attentional demands of the cognitive training intervention without the additional cognitive load.

#### Cognitive training

2.5.2

The participants will complete a series of adaptive multi-domain cognitive tasks (including executive function and working memory tasks) using BrainHQ (Posit Science USA), whilst seated quietly at a desk with minimal distraction. The software adjusts the difficulty to user performance, considering moderators such as learning and fatigue. Each task consists of several levels that broadly increase in complexity in a non-linear manner to maintain a challenging stimulus, by increasing distractors, decreasing target sizes, and reducing response time. Participant performance will be compared against proprietary normative data and required a 70–80% criterion threshold to be met across the training block (typically 10–30 trials) to reveal a new level in the subsequent training session. Lower performance requires participants to repeat the same level on the next attempt. Such multi-domain cognitive training tools provide the most efficacious approach to global and domain specific cognitive benefits (28). The specific cognitive training tools from BrainHQ employed align with domains of cognitive function that may be impacted in this population, which includes: Double Decision (assessing visual processing speed and selective attention), Target Tracker (assessing spatial attention), Hawk Eye (assessing visual speed and attention), Juggle Factor (assessing visuospatial memory and tracking), Scene Crasher (assessing visual working memory) and Eye for Detail (assessing visual processing speed and visual working memory). Participants are given the goal of attaining 20 levels per week of cognitive training from Week 3 onwards (i.e., the maximum exposure of cognitive training).

#### Concurrent cognitive and physical training

2.5.3

The participants will undertake the same cognitive training and physical training interventions described above but delivered simultaneously. Figure 3 depicts the setup of this intervention. The touchscreen utilized for responses (task-dependent) will be fixed to the stationary bike utilizing a customized gooseneck attachment to the handlebar.

**Figure 3 fig3:**
[figure not shown]
Concurrent training intervention set up showing the attachment of the tablet to the bike.

#### Wait-list control

2.5.4

Participants in the wait-list control will have no contact with the research team outside of a fortnightly check-in over the phone to maintain engagement with the study. The phone calls aim to capture engagement in any kind of physical or cognitive activity within that fortnight, as is described in detail below. Participants will have the option to complete any of the other intervention arms following the initial 8-week intervention period of usual care and subsequent assessments.

### Assessments

2.6

The initial session will be used to confirm eligibility, gain consent, and complete baseline questionnaires. Following this, participants will attend the laboratory on a separate occasion to complete pre-intervention objective assessments. On arrival, anthropometric measures (height, weight, waist and hip circumference, and blood pressure) will be obtained, followed by the objective cognitive assessments, and the aerobic fitness assessment (both of which are detailed below). A university-trained clinical exercise physiologist will monitor all assessments (including electrocardiogram surveillance during the aerobic fitness test), which will act as an additional screening into the trial. Following this assessment procedure, participants will be provided with a referral to attend a local pathology clinic in the ACT to obtain a blood sample as part of the secondary outcome measures. Timing of assessments will consider fatigue, training, and time of day effects within dedicated research spaces at the University of Canberra. Post-intervention assessments will follow the same format after the completion of the 8-week intervention period.

#### Primary outcomes

2.6.1

Primary outcome measures comprise of feasibility measures in accordance with the first aim. These feasibility measures form the progression criteria, as summarized below.

### Progression criteria

2.6.2

This pilot clinical trial will provide insights (e.g., feasibility, statistical power, effect estimates) which will guide the development of a larger-scale clinical trial that will aim to improve the cognitive and fatigue outcomes in men affected by prostate cancer receiving ADT. Clinical trial progression criterion as recommended (39), accounts for recruitment success, adherence, adverse events, subjective accounts of the intervention, and the likelihood of benefit. Table 1 provides an overview of the criterion and decision-making related to the progression to a larger trial—each of which are detailed below. As indicated in the progression criteria, further feasibility work may be required depending on the findings of the present study. Mixed findings will be interpreted holistically across criteria, with priority given to safety and acceptability to inform progression and protocol refinement.

**Table 1 tab1:** Suggested progression criteria for seeking funding for a larger trial.

Outcome measures	Not to progress to clinical trial	Potentially progress with revisions	Progress to clinical trial
Recruitment	Project recruits <50% sample size in designated time frame. Consider alternate designs/qualitative work to understand why.	Project recruits <100% sample size in designated time frame. Evaluate multi-site/locality implications for large trial. Consider qualitative work to understand best recruitment strategies/barriers.	Project recruits designated numbers in proposed timeframe. Consider locality/ies for larger trial based on power analysis.
Adherence	Adherence is <50%.	Adherence is 50–65%, consider factors to increase adherence.	Adherence is higher than 65%.
Adverse Events	Occurrence of any significant adverse events deemed to relate directly to the intervention.	Occurrence minor adverse events (e.g., increased fatigue) consider if protocol changes can be made.	No adverse events reported.
Subjective participant experience	Subjective accounts are overall negative.	Subjective accounts are neutral. Consider how participant experience could be managed to improve subjective outcomes.	Subjective accounts are overall favorable. (>50% positive descriptive data, supported qualitatively)
Benefit likelihood	If results suggest likely harm across most cognitive outcomes (e.g., Consistent negative effect sizes)	Results suggest potential harm. Consider changes to protocol.	Results are neutral or positive in effect size across most cognitive outcomes. Proceed to larger trial.

#### Recruitment success

2.6.3

Recruitment success will be measured by recording recruited participant numbers within the recruitment time frame. This will be assessed on a rolling basis to evaluate progress against the target number of participants. Specifics of our recruitment strategies will be described for future reference including details of the most effective recruitment strategies.

#### Adherence

2.6.4

Adherence retention, and withdrawal will be recorded throughout the study, as well as study compliance. Participants will sign against attendance for training sessions and subsequent session reminders will be provided. Participants will be permitted to make up a “missed” session in the week that the session is missed, if there is time to do so (that is, reschedule a session within the same 7-day period).

Sessions throughout the course of the intervention will be booked in advance, and participants will be financially reimbursed in the form of a gift card for their time investment in the study and to assist with retention. The number of withdrawals from the study will be recorded with reasons documented (if provided).

Compliance in the sessions involving physical training, cognitive training or concurrent training will be assessed to ensure participants are meeting the parameters required of the allocated intervention. For the interventions with a physical training component, this involves ensuring participants exercise at the desired intensity (heart rate between 60 and 70% of their age-predicted heart rate maximum and/or a rate of perceived exertion that corresponds to moderate intensity on the 6–20 Borg scale (11–13) and for interventions involving cognitive training, this involves achieving the target of 20 levels per week.

#### Adverse events

2.6.5

When a participant presents for an intervention session, before commencing training, they will be asked about the intervention subjective acceptability (detailed below), as well as whether they have experienced any adverse events in relation to the intervention. Any record of adverse events will be categorized in accordance with the Common Terminology Criteria for Adverse Events (40) as Grade 1—Mild (asymptomatic or mild symptoms; clinical or diagnostic observation only; intervention not required) through to Grade 5 (death related to adverse event).

Serious adverse events classified as events graded 3, 4 or 5 will be recorded if resulting from the administration of an intervention session within this study and will result in the modification of intervention as appropriate. Events that are serious but are not related to the intervention will not be recorded as serious adverse events. Any adverse events or safety-related withdrawals will be reviewed and managed in accordance with study protocols and relevant ethical guidelines.

Protocol modifications following an adverse event will be considered on a case-by-case basis in consultation with the clinical and medical staff involved in the study. Adverse events will be reviewed periodically, and decisions regarding continued participant involvement will be made accordingly. All intervention-related events and any resulting modifications will be reported in the final study publication.

Alternative causes such as the natural history of the underlying disease, other risk factors, and the temporal relationship of the event to the intervention are considered. The Chief Investigator will report serious adverse events related to the intervention (requiring medical or pharmaceutical intervention or hospital admission) to the University of Canberra Human Research Ethics Committee within 24 h.

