#### Cardiorespiratory fitness

2.6.11

Aerobic fitness will be assessed using the Åstrand Rhyming submaximal exercise test on a recumbent cycle ergometer (Lode, The Netherlands). This protocol is described in detail elsewhere (55), but briefly, this single-stage test commences at 50 watts of resistance, with periodic increases in resistance if heart rate is below 120 beats per minute (56, 57). Throughout the 6-min assessment, the participant is required to maintain a pedal rate of 50 revolutions per minute (56). Heart rate obtained during minute 5 and 6 of the test are averaged together to use in the nomogram and equation to predict VO_2_max (57).

Given the population of interest, and the likelihood of existing factors that influence heart rate including cardiovascular comorbidities and various medications, participants in this study may not be able to achieve the desired heart rate, but their RPE on the 6 to 20 Borg scale should reflect a submaximal intensity between 11 and 13.

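### The serious-event rule covers only harm from the training intervention, so a grade 3–5 event caused by a trial assessment, chiefly the cycle fitness test, has no place in the serious-event record or the 24-hour ethics report

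*Protocol article*

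**What the plan says.** All from the protocol article.

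- **Recording (2.6.5 Adverse events).** Serious adverse events are defined as CTCAE grades 3, 4 or 5, and they "will be recorded if resulting from the administration of an intervention session within this study".
- **Exclusion (same section).** "Events that are serious but are not related to the intervention will not be recorded as serious adverse events".
- **Expedited report (same section).** "The Chief Investigator will report serious adverse events related to the intervention" to the ethics committee within 24 hours, with a further qualifier about medical or pharmaceutical treatment or hospital admission.
- **Publication (same section).** The commitment to publish covers intervention-related events and the modifications that follow from them.
- **What the intervention is (2.5 Intervention).** "The training interventions will consist of 2 sessions per week for 8 weeks conducted on non-consecutive days". The subsections that follow describe the three training arms and the wait-list.
- **What lies outside it (2.6 Assessments, 2.6.11 Cardiorespiratory fitness, Blood biomarkers).** "Aerobic fitness will be assessed using the Åstrand Rhyming submaximal exercise test on a recumbent cycle ergometer". A blood sample is taken at a community pathology clinic. Both are done before and after the 8-week period.

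**The concern.** The rule is drawn around the intervention, but men in this trial are exposed to more than the intervention. Every participant is asked to exercise on an ergometer at two assessment visits because he is in the trial. Harm from that test is harm caused by the trial, and it does not result from a training session.

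The protocol itself treats the test as needing care. Section 2.6 provides for clinical exercise physiologist monitoring, "including electrocardiogram surveillance during the aerobic fitness test", and section 2.6.11 refers to "the likelihood of existing factors that influence heart rate including cardiovascular comorbidities and various medications". Having foreseen cardiac vulnerability during the test, the plan then words its serious-event rule so that an event there falls outside it.

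At stake are the completeness of the serious-event record, prompt notice to the ethics committee, and the safety account that readers and the designers of a larger trial will rely on. Section 2.6.2 gives safety priority when progression findings are mixed, so the record ought to hold all serious harm that the trial causes.

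**Working it through.** The plan gives no figure to reproduce. The check is whether any text brings an assessment-related event back under the rule.

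1. **Is the cycle test an intervention session?** No. Section 2.5 defines the sessions as the twice-weekly training. The test is described under 2.6 and 2.6.11 and is done before and after the training or wait-list period.

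2. **Could a test-related event be related to the intervention in a looser sense?** The recording sentence refers to an intervention session. The exclusion and 24-hour sentences use the slightly wider idea of relation to the intervention. Neither names assessments. For the baseline test the wider reading fails outright: under 2.3 the allocation envelope stays closed until baseline testing is complete, so the man has no assigned intervention to which the event could relate. For the post-intervention test in a wait-list man, no training has been given in the assessed period.

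3. **Does any other sentence in 2.6.5 supply the duty?** One sentence says that any adverse events and safety-related withdrawals will be reviewed and managed under study protocols and ethical guidelines. Others say that recorded events are graded and periodically reviewed. None requires recording as serious, a 24-hour report or publication, and none overrides the express exclusion.

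4. **Is the question put to participants any wider?** No. They are asked "whether they have experienced any adverse events in relation to the intervention".

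5. **How much exposure lies outside the rule?** Inputs are the 76-man target (2.2), 19 per arm (2.4) and two tests per man (2.6).
 - Planned tests: 76 × 2 = 152.
 - Before allocation: 76.
 - After allocation: 76, of which 19 are in wait-list men.

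 These counts assume full recruitment and retention. Dropout lowers them. Men tested at baseline but never randomised raise the pre-allocation count, because 2.6 treats these assessments as a further screen into the trial.

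6. **Where would a baseline event go?** A man harmed at the baseline test might never be randomised. He would then be missing from the serious-event record and also from the analysis set in 2.7, which comprises randomised participants.

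**The case against.** The strongest reply is that the gap is narrow. The test is a 6-minute, single-stage, submaximal procedure in which resistance rises only if heart rate is below a set level. It is supervised throughout. The exclusion says that unrelated events are not recorded *as serious adverse events*; it does not say they go unrecorded. The ethical guidelines to which 2.6.5 points, and any fuller protocol, are not shown and may impose a reporting duty of their own. Section 2.6.5 also serves a progression criterion about the intervention, for which an intervention-related definition is apt.

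Much of this stands, and it limits the consequences. Three stronger inferences are therefore not supported:

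- *Harm in wait-list men would go unseen.* Staff monitor every fitness test, and 2.6.4 logs withdrawals with reasons where given. The event would be witnessed. What is missing is its classification and reporting route.
- *Both tests in wait-list men are wait-list exposure.* The first is done before allocation, so only about 19 tests are done by men already allocated to that arm.
- *The test count can be turned into an upper limit on test risk.* The tests are paired within men, the second is done only by those who came through the first, and estimating that risk is not an aim of the trial.

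The reply does not remove the point. If outside rules require wider reporting, the protocol is narrower than the duty, and staff who follow it would under-report. Nor is this detail left to a fuller document: the article states the exclusion expressly.

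**Conclusion.** The point holds as a gap in the scope of the safety rule. Followed as written, section 2.6.5 leaves a grade 3 to 5 event caused by a trial assessment out of the serious-event record, the 24-hour ethics report and the commitment to publish. The cycle test is the procedure that matters. The blood draw is formally in the same position, but nothing in the document suggests that serious events from it are likely.

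The size is modest. About 152 planned tests are affected if all 76 men complete both, half of them before allocation. The document gives no event rate, and serious events in a supervised submaximal test are presumably rare. A reader might infer that progression decisions are affected. They are not, provided the adverse-event row of Table 1 is applied to intervention-related events. Its stop column says so explicitly; the other two columns do not. No sample size or effect estimate changes.

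The conclusion rests on reading the intervention as the training described in 2.5, and on no unseen text widening the rule.

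**What to change.** In 2.6.5, reword the recording condition to *resulting from any study procedure (assessment or intervention session)*, and bring the exclusion sentence into line with it. Add a field to the event form for the source procedure. Apply the same 24-hour ethics report, and the same commitment to publish, to events from any study procedure.

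Keep the adverse-event row of Table 1 for intervention-related events, and state this for all three columns. Report procedure-related events in a separate table: baseline events among all consented men, before allocation and without an arm; post-intervention events by arm. A pre-intervention blood-draw event can be placed according to whether allocation had yet taken place.

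The cost is a wording amendment through the ethics committee, one extra form field, and possibly a slightly less favourable overall safety count. No assessment, training session or clinical rule has to change.

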**Figure 2 fig2:**
[figure not shown]
SPIRIT Figure. *Feasibility measures including adverse events and adherence will be monitored throughout the intervention period. Recruitment success will be monitored on a 6 monthly basis and subjective acceptability of the study will be captured at the end of the 8-week intervention for each participant via an exit survey.

The experimental protocol will consist of (1) eligibility screening and informed consent, (2) baseline cognitive health, fatigue, quality of life and physical activity questionnaires, (3) pre-intervention objective cognitive and physical assessments, (4) 8-week training intervention with mid-point questionnaires and (5) post-intervention questionnaires and objective testing, as per Figure 2.

This study has been approved by the University of Canberra Human Research Ethics Committee (#11955). Any amendments to the protocol will be approved by the University of Canberra Human Research Ethics Committee and subsequently submitted to the Australia and New Zealand Clinical Trial registry ACTRN12623000767606 and the funder.

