### Randomization, group allocation, and blinding

2.3

All participants who give consent and fulfill the inclusion criteria will be stratified by age (+/− 65 years) and then randomly allocated in a 1:1:1:1 ratio to one of four treatment arms: (1) physical training, (2) cognitive training, (3) concurrent cognitive and physical training, or, (4) wait-list control. Randomization will use a computer-generated sequence of numbers in blocks of variable sizes in a 1:1:1:1 ratio by a researcher not directly involved in the study. Allocation concealment will be ensured using sequentially numbered, opaque, sealed envelopes prepared by this independent researcher and kept inaccessible to recruitment and assessment staff until completion of baseline testing. After baseline testing (outlined below), this envelope with the group allocation will be delivered to the participant and training staff. Once opened, the training staff will provide information to the participant about the allocated intervention arm. Blinding of intervention allocation is not possible for any participant or the training staff. Team members completing the post-intervention assessments will be blinded to participant group allocation and will not be involved in data analysis. Treating clinicians involved in referring potential participants to the study (including author GP) will be blinded to whether potential participants choose to engage with the study.

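### The stated adverse-event enquiry is session-based and filtered by relatedness, with none described for the wait-list arm, so a primary progression criterion has no untreated rate and is easier to pass

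*Protocol article*

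**What the plan says.** **Where and how events are elicited (section 2.6.5).** The enquiry is tied to attendance: "When a participant presents for an intervention session, before commencing training, they will be asked about the intervention subjective acceptability". In the same exchange he is asked "whether they have experienced any adverse events in relation to the intervention".

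**What counts as serious (section 2.6.5).** Events of CTCAE grade 3 to 5 "will be recorded if resulting from the administration of an intervention session within this study". The next sentence closes the category: "Events that are serious but are not related to the intervention will not be recorded as serious adverse events".

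**Who judges (section 2.3).** "Blinding of intervention allocation is not possible for any participant or the training staff".

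**The wait-list arm (section 2.5.4).** During the 8 weeks these men "will have no contact with the research team outside of a fortnightly check-in over the phone to maintain engagement with the study". On content: "The phone calls aim to capture engagement in any kind of physical or cognitive activity within that fortnight". No adverse-event question is mentioned.

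**Other routes.** The Figure 2 legend says: "Feasibility measures including adverse events and adherence will be monitored throughout the intervention period". It also places an exit survey at the end of the 8 weeks, and section 2.6.6 lists adverse effects among the perceptions that survey covers. Section 2.6.4 documents reasons for withdrawal where a man offers one, and section 2.6.5 has safety-related withdrawals reviewed.

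**How the data are used (sections 2.6.1 and 2.6.2, Table 1).** The feasibility measures are the primary outcomes. The least favourable category is met by a significant event attributed directly to the intervention. The most favourable requires that no adverse event be reported. Mixed findings are resolved with priority to safety and acceptability.

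**The concern.** Relatedness is normally judged after an event has been recorded. Here it acts twice before or during recording: once in the question put to the participant, and again in the rule for the serious-event record. Both judgements are made in an open-label setting. Section 2.6.5 does require alternative causes to be weighed, but an event that the man himself does not connect with training may never reach that review.

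A randomised control arm is the natural check on such judgements. The Background says that men on ADT commonly have distressing fatigue and a raised predisposition to cardiovascular disease, diabetes and depression. Section 2.6.11 expects cardiovascular comorbidity and medication. Some events will therefore occur without any training. If the wait-list arm is not asked, the trial cannot show how many.

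The most favourable category in Table 1 carries no relatedness limit, whereas the enquiry that feeds it does. Any event not captured moves the result towards progression, on the criterion that is to take priority when findings are mixed.

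**Working it through.** The plan states no figure on this point, so there is none to reproduce. The check is mainly a reading of the text by arm and by period, followed by a small illustration.

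**1. Coverage by arm and period**

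| Period | Three trained arms | Wait-list arm |
|---|---|---|
| During the 8 weeks | Question before each session, limited to related events (2.6.5) | Fortnightly call, described as capturing activity (2.5.4) |
| After the last session | Exit-survey perceptions (Figure 2 legend, 2.6.6); in-person post-assessment with no adverse-event question stated (2.6) | Same contacts; no adverse-event question stated |
| At withdrawal | Reason if offered (2.6.4); safety-related withdrawals reviewed (2.6.5) | Reason if offered (2.6.4) |

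- Sessions: 8 weeks × 2 = 16. Each enquiry comes before training, so it looks back to the previous session. Events after sessions 1 to 15 have a later enquiry; events after session 16 have none of this kind.
- Arm sizes: 19 per arm (section 2.4), so 3 × 19 = 57 trained and 19 wait-list. 19/76 = 25% have no described enquiry.
- The exit survey is used to classify overall experience as favourable or not. It is not described as yielding CTCAE-graded events.

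**2. Effect of under-capture on the most favourable category**

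Let p be the true risk per man of at least one event and c the share captured. The documents give neither, so both are assumptions, shown over a range. With n men,

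P(no event recorded) = (1 − p·c)^n.

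| p | n = 19, c = 1 | n = 19, c = 0.8 | n = 19, c = 0.5 | n = 57, c = 1 | n = 57, c = 0.5 |
|---|---|---|---|---|---|
| 5% | 0.38 | 0.46 | 0.62 | 0.054 | 0.24 |
| 10% | 0.14 | 0.21 | 0.38 | 0.0025 | 0.054 |
| 20% | 0.014 | 0.036 | 0.14 | <0.001 | 0.0025 |

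Example: p = 10%, c = 0.5, n = 19 gives (1 − 0.05)^19 = 0.38, against (1 − 0.10)^19 = 0.14 with full capture.

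**3. What a zero count can show**

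Even with full capture, no events in n men leaves a one-sided 95% upper bound of 1 − 0.05^(1/n): 14.6% for n = 19 and 5.1% for n = 57. With incomplete capture these bounds apply to the risk of a recorded event, not to the risk of an event.

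**The case against.** The strongest reply is that the article condenses a fuller protocol. The legend to Figure 2 promises monitoring throughout, the exit survey asks about adverse effects, exercise physiologists supervise every session, and the additional files are not shown. This stands in part. Whether the fuller documents ask wait-list men about adverse events cannot be seen, and that gap is inferred from how the calls are described. It does not reach the relatedness filter or the serious-event rule. Those are positive statements, and fuller detail could not remove them without contradicting the article.

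A second reply is that the least favourable category in Table 1 is meant to be an attribution test, and that 19 per arm is too few for a useful rate comparison. It is fair that such a comparison would be imprecise, and attribution may properly drive that category. The most favourable category, however, is not limited to related events, and a control count is still the only untreated reference the trial could have. SF-12 vitality and FACT-G give some background on symptoms such as fatigue, but they are not event records.

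Three stronger readings are tempting and are not supported:

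- A reader might infer that events after the last session, or those leading to drop-out, are lost. The exit survey, the documented withdrawal reasons and the review of safety-related withdrawals are routes to them. Those routes are voluntary or ungraded, so under-capture is possible, but loss is not established.
- A reader might infer that unrelated serious events go unrecorded altogether. The sentence bars recording them as serious; it does not say they are not recorded at all.
- A reader might infer that no comparison is possible. The three trained arms share the same enquiry and can be compared with one another. What is absent is an untreated rate.

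**Conclusion.** The point holds in this limited form and should be addressed before the progression decision relies on adverse-event counts. As written, the active enquiry is made at training sessions and filtered by relatedness. Entry to the serious-event record depends on an open-label attribution, and a quarter of the sample has no described enquiry. Capture after session 16 and at drop-out is weaker than during training, by an amount the documents do not allow to be estimated.

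The direction is clear: under-capture favours the category for progressing. The size is illustrative only. At an assumed 10% risk in one arm of 19, halving capture raises the chance of a clean record from 0.14 to 0.38. Across 57 trained men it rises from 0.0025 to 0.054.

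The conclusion assumes that the Figure 2 schedule and the additional files add no adverse-event question to the wait-list calls, the post-assessment or the withdrawal contact. If they do, the wait-list and end-of-study parts fall away, and the relatedness filter remains.

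**What to change.** - Put one open adverse-event question, with no reference to cause, to all four arms: before each session in the trained arms, in the existing fortnightly calls for the wait-list arm, and for everyone at post-assessment and at withdrawal.
- At post-assessment, have it asked by staff other than the outcome assessors, who section 2.3 keeps blind to allocation.
- Record every event, with CTCAE grade, seriousness and relatedness as separate fields.
- Report counts by randomised arm, overall and for related events.
- Leave the related-event criterion for not progressing in Table 1 as it is.
- While editing, reconcile Table 1, which gives increased fatigue as an example of a minor adverse event, with section 2.6.9, which reports CTCAE-graded fatigue as a secondary outcome and not as an adverse event. Otherwise it is unclear which fatigue reports count towards the criterion.

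The cost is one question at contacts that already take place and more unrelated events to log. No visit is added. Between-arm comparisons will remain imprecise at 19 per arm and should be presented descriptively.
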